## **7.4 Outcomes**

Primary outcomes are number of chronic medications and percent of individuals on one or more potentially inappropriate medications (PIMS).

Secondary outcomes to be addressed following primary analyses include the number of starts of potentially inappropriate medicines, dose reductions for selected potentially inappropriate medications (benzodiazepines, opiates, and antipsychotics), rates of adverse drug events (falls, hemorrhagic events, and hypoglycemic events), activities of daily living as reported in the Medicare Health Risk Assessment, and skilled nursing facility, hospital, and emergency department admissions.

## **7.5 Data Analyses**

The distributions of all variables, including outcomes, predictors, and covariates, will be examined univariately for data integrity, missing data, and outliers. Outliers will be explored with limited chart review. Data transformation may be conducted as appropriate. We will then assess bivariate associations between independent variables, covariates and primary and secondary outcomes. Multilevel models will be used to account for the clinic level randomization and clinic level intervention as well as adjusting for covariates. The models will include random effects for clinic and fixed effects for intervention versus delayed control and time (baseline or 1-year). We will assess possible nesting of patients within providers; however, most patients see multiple medical doctors, physician assistants and/or nurse practitioners. Change in medication use will be estimated in models that examine medication outcomes at follow-up, adjust for baseline medication use and estimate change by including an interaction term for intervention by time. These models can include baseline patient risk factors as well as provider characteristics to account for imbalanced baseline covariates between clinics. Primary analyses will focus on all members meeting eligibility at either baseline or follow-up time periods (6-months and 1 year) and patient indicators will be included as random effects to identify which patients have information at both baseline and follow up versus baseline or follow up only. Secondary analyses will examine the subset of patients who have both baseline and follow-up data available. We expect these secondary analyses will have comparable conclusions but if differences are seen we will explore potential explanations such as unexpected differential deaths or loss-to-follow-up or whether differences in the patient populations might suggest effect modifiers. For change in number of chronic medications, we expect to use Poisson regression mixed models while for change in the proportion of patients on PIMs, and some secondary outcomes, nonlinear

mixed model techniques will be needed. These models already accommodate data that are missing at random (MAR), which will be adequate for some missing covariate data. For items unlikely to be MAR, such as missing questionnaire responses, we will explore multiple imputation methods to estimate missing scores.

We will examine effects of the intervention within the following prespecified subgroups: 1) members who received a higher dose of the intervention (e.g., brochure and more than one visit), 2) members on higher numbers of medications at baseline (7 or more medications), and 3) individuals with MCI vs. ADRD. We anticipate missing data on at least 50% of the cohort for secondary outcome measures of patient reported outcomes of ADLs and health related quality of life and analyses will use a three-pronged approach. First, we will describe persons with and without these measurements by covariates such as age, health care utilization and co-morbidities. Second, we will use multiple imputation to create replicate datasets with plausible values using estimation models that include covariates and the dependent variables themselves. Because multiple imputation can only address data that are missing at random, i.e. missing data explained by measured covariates, our third step will be sensitivity analyses using methods such as pattern mixture models that aid in examining the consistency of results within groups of patients with similar patterns of missing data.

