## **2 STUDY DESIGN**

The study will be a pragmatic, cluster randomized trial with randomization at the level of the clinic and a delayed control group. Clinics will be randomized in blocks of two based on the number of eligible patients per clinic.

Primary outcomes will be total number of medications prescribed and percent of individuals with >1 PIMs prescribed at 6- and 12-months following intervention initiation. Outcomes will be measured with pharmacy dispensing data. PIMs will be based on the Beers List additionally including opioid medications.

Secondary outcomes will include rates of selected adverse drug events (falls, bleeding episodes,

hypoglycemic episodes), dose reductions for selected potentially inappropriate medications (benzodiazepines, opioids, antipsychotics), hospital, emergency department and skilled nursing facility utilization, and activities of daily living reported in the Medicare Health Risk Assessment. Secondary outcomes will be examined following primary outcome analyses.

The eligible patient population will be all KP members ages 65 or greater with a diagnosis of ADRD or MCI from either ICD visit codes or documentation on the problem list, plus at least one other chronic condition. Patients must also be taking 5 or more chronic medications and have a PCP in the KPCO Denver-Boulder area. Of this eligible population, those who schedule a visit with their PCP in an intervention clinic during the study period will receive the intervention.

Exclusion criteria: As the pragmatic trial will be based in primary care clinics, individuals residing in long term care facilities, enrolled in hospice care, or receiving home-based primary care services will be excluded.

The clinician population for the study will be all PCPs who care for adult patients at intervention clinics.

The study setting will be 18 primary care clinics in the KPCO Denver-Boulder geographic area.

The intervention duration will be from April 2019 – February 2022. The initial intervention will run 12 months from March 2019 through April 2020. The intervention for the delayed control group will run from ~September 2021 through ~February 2022. Outcomes for the initial intervention group will be measured at 6 months and 12 months.

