rPATD: revised Patients' Attitudes Towards Deprescribing 9-question questionnaire and one question on who completed it. Collected from patients/ care partners as part of the intervention on paper and returned by mail.

PPMD: Physicians Perception of Medication Discontinuation. Collected on paper during the initial portion of the clinician intervention – presentation at clinician team meeting.

Physician specialty: Will be obtained from Colorado Permanente Medical Group data sources.

Time and interval definitions: Enrollment, Baseline, and/or Randomization:

Baseline: The baseline point will be defined as the time at which patients are identified as having an upcoming appointment with their PCP and are mailed the intervention materials. For patients who receive second mailings in advance of a subsequent PCP visit, baseline will remain their first visit but second mailings will be tracked and examined in selected analyses. Baseline for patients in the control clinics will be the date of the first PCP appointment during the initial intervention period. Identical methods will be used to screen control patients for eligibility and identify upcoming visits as described above to ensure comparable identification.

Randomization: Randomization will be at the clinic level and will be stratified by clinic size. (See analytic plan below.)

Follow-up Visits: Data extractions do not depend on follow up visits in this study. Dates for follow up measurements described in the Evaluations Table will be relative to baseline and data will be extracted from the VDW as described above.

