### **7.2 Sample Size and Randomization**

#### **Sample Size and Randomization**

There will be 9 intervention clinics and 9 control (delayed intervention clinics). We estimated power using members who would be eligible for the intervention in November 2018. Feasibility data for that cohort showed a median of 5 visits in the prior year with 99% having at least one visit and 80% scheduling a visit at least 7 days in advance. Patient materials are sent in advance of visits only for appointments made at

least 7 days before a visit, therefore, we anticipate approximately 80% of the eligible intervention population will receive mailings during the study period.

We identified 3,671 eligible members with numbers per clinic ranging from 60 to 350. For analyses of counts of medications, we will have > 80% power to detect a decrease of -0.70 (i.e. < 1 medication; power from difference in two Poisson rates in cluster-randomized trial given event rate of 6.8 and intraclass correlation coefficient (ICC)=0.01). We will be examining selected subgroups of interest, for example cohort members receiving a higher dose of the intervention or a restricted cohort with more severe dementia. Both of these comparisons could reasonably retain ~70% of the intervention cohort to contrast to the control cohort and we would be able to detect a decrease of 1.4 medications even if ICC was doubled (i.e. 0.02). Comparisons of proportions of members on a PIM will be able to detect a decrease to 29.0% or less for the intervention clinics compared to the expected rate of 35.8% for the control clinics.

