#### 7.2.1 Treatment assignment procedures

The intervention will be a cluster randomized trial delivered at the clinic level with a delayed control design so that all potentially eligible KPCO members will have the opportunity to receive enhanced medication management. Outcomes will be measured at the level of the individual. Clinics will be randomized in blocks of two based on the number of eligible patents. In past experience this has balanced patient characteristics, but we will confirm comparability of the key variables for this study between the intervention and delayed control clinics and consider different blocking schemes if appropriate. Limited remaining differences will be described and adjusted for in statistical analyses.

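### Clinics are randomised in size-based blocks of two, but the model terms listed in 7.5 include neither block nor clinic size; one prespecified size term would recover a small amount of precision at almost no cost.

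*Protocol*

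**What the plan says.** On allocation, Protocol section 2 states: "Clinics will be randomized in blocks of two based on the number of eligible patients per clinic". Section 7.2.1 repeats this. Section 4.2, under its time and interval definitions, puts it as stratification and points forward: "Randomization will be at the clinic level and will be stratified by clinic size. (See analytic plan below".) Section 3.1 describes the blocking as resting on clinic size and the number of potentially eligible patients.

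On size, section 7.2 states: "There will be 9 intervention clinics and 9 control (delayed intervention clinics"), and "We identified 3,671 eligible members with numbers per clinic ranging from 60 to 350".

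On analysis, section 7.5 states: "The models will include random effects for clinic and fixed effects for intervention versus delayed control and time (baseline or 1-year"). The same section adjusts for baseline medication use, reads change from an intervention-by-time interaction and adds patient random effects. It allows covariates in general terms, and patient and provider characteristics where these are imbalanced between clinics. Section 7.2.1 likewise says that differences remaining after blocking will be adjusted for. Neither section names block or clinic size as a model term.

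**The concern.** A design that blocks on a variable removes variation linked to that variable from the comparison of arms. If the model has no term for it, that variation can stay in the error term. The standard error is then larger than it need be, the test runs below its nominal 5%, and some power is given away.

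The adjustment routes in 7.2.1 and 7.5 are triggered by imbalance. Clinic size should be balanced by construction, so they would not naturally bring it in. A reader who follows the pointer in section 4.2 to the analytic plan finds a listed model without the factor on which the clinics were randomised.

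At stake is efficiency, mainly for the PIM outcome, and agreement between design and analysis.

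**Working it through.** **The plan's own PIM figure.** Inputs from 7.2: 3,671 members, 18 clinics, 35.8% against 29.0%. ICC 0.01 is stated for the medication count ("power from difference in two Poisson rates in cluster-randomized trial given event rate of 6.8 and intraclass correlation coefficient (ICC)=0.01") and is carried over to PIM as an assumption. Alpha and sidedness are not stated for PIM.

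- Mean clinic size 3,671/18 = 204; design effect 1 + 203 × 0.01 = 3.03; members per arm 3,671/2 = 1,835.5.
- SE = √[(0.358 × 0.642 + 0.290 × 0.710) × 3.03/1,835.5] = √(0.4357 × 3.03/1,835.5) = 0.0268; 0.068/0.0268 = 2.54.
- Power is about 81% at one-sided 5% and about 72% at two-sided 5%.

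The stated 29.0% therefore reproduces from an unmatched formula (one-sided). It appears to take no credit for matching, so omitting block does not undercut it.

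**Set-up for the comparison.** Eighteen evenly spaced sizes scaled to total 3,671 (about 60 to 348; mean of 1/m = 0.00634), paired by size, one clinic per pair allocated at random. V = 0.324 × 0.676 = 0.219, where 0.324 is the midpoint of the two PIM proportions. Difference 0.068, two-sided 5%. The test is a clinic-level t-test on 16 df, or 15 df with log size added. The share s of between-clinic variance linked to size is not in the Protocol, so it is varied.

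**(a) Follow-up means, no baseline.** Average clinic variance = ICC·V + (1 − ICC)·V·mean(1/m) = 0.00219 + 0.00137 = 0.00356. SE = √(2 × 0.00356/9) = 0.0281; 0.068/0.0281 = 2.42. With s = 0.5 removed by a size term: 0.00110 + 0.00137 = 0.00247; SE = 0.0234; ratio 2.90.

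**(b) Change from baseline, closer to 7.5.** Average variance of clinic change = 2·ICC·V·(1 − c) + 2·(1 − ICC)·V·(1 − w)·mean(1/m), where c is the cluster autocorrelation and w the within-patient correlation, both assumed.

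- c = 1, w = 0.5: 0 + 0.00137; SE = 0.0175; ratio 3.9. No clinic component is left for size to explain.
- c = 0.8, w = 0.5: 0.00088 + 0.00137 = 0.00225; SE = 0.0224; ratio 3.04. With half the drift tied to size and removed: 0.00044 + 0.00137 = 0.00181; SE = 0.0201; ratio 3.4.

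Simulated PIM results (40,000 trials per setting; w = 0.5 in the change rows):

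| Analysis | Size share | Type I error without size | Power without size | Power with log size |
|---|---|---|---|---|
| Follow-up only | 0 | 5.2% | 62.0% | 62.0% |
| Follow-up only | 0.25 | 3.4% | 62.6% | 69.2% |
| Follow-up only | 0.5 | 1.9% | 62.8% | 77.1% |
| Change, c = 1 | any | 5.1% | 95.0% | 95.2% |
| Change, c = 0.9 | 0 | about 5% | 88.8% | 89.0% |
| Change, c = 0.9 | 0.5 | 3.7% | 89.6% | 92.1% |
| Change, c = 0.8 | 0.5 | 2.8% | 82.9% | 88.3% |

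Taking w = 0.7, or adjusting follow-up for baseline rather than taking change, keeps the gain in the same range of about 0 to 5 points.

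**Nine block effects instead of one size term.** In setting (a) at s = 0, pair effects (8 df) lower power from 62.0% to 56.6%. In a separate calculation with equal clinic sizes they break even only when block explains about 20% of between-clinic variance.

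**Medication count.** Power for a 0.70 decrease is 98.7% to 100% with or without the size term, even on follow-up means, so the only possible gain is a narrower interval.

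**The case against.** The strongest case is that the listed model already does most of what blocking would offer. With baseline in the model and the effect read from intervention-by-time, stable clinic differences cancel, including those linked to size. A size term then helps only if clinic effects drift over time and the drift follows size. This stands, and it limits the claim to a few points.

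A reader might infer that intervals are certainly too wide and that PIM power falls from 77% to 63%. The documents do not support that. The pair of figures belongs to follow-up means without baseline adjustment, which is not the analysis in 7.5, and to an assumed size share of 0.5. The Protocol nowhere says that size predicts PIM use. Section 7.2.1 justifies blocking by past balance of patient characteristics, not by precision.

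The remedy also has limits, and this stands too. If the variance shared within blocks is not roughly linear in size, log size recovers little: 64.5% to 65.5% on follow-up means at share 0.5, with type I error still about 2.1%.

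Finally, 7.5 is open to covariates, and a full list may sit in a statistical analysis plan that is not at hand. That weakens the point without removing it. The Protocol itself lists the model's design terms and sends the reader from the stratification to the analysis, and the covariate routes it spells out depend on imbalance.

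**Conclusion.** The point holds as a minor matter of efficiency and consistency. The trial randomises on clinic size, and the listed model does not carry it. Any resulting error is in the conservative direction: type I error is about 3% to 5% under the baseline-adjusted or change analysis. The PIM power gain from one size term is about 0 to 5 points, and near zero if clinic effects are stable and the effect is read purely from intervention-by-time.

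These sizes rest on assumptions that the Protocol does not supply: two-sided 5% and ICC 0.01 for PIM, within-patient correlation 0.5 to 0.7, cluster autocorrelation 0.8 to 0.9, size shares of 0 to 0.5, and a clinic-level approximation to the mixed model. Validity is not threatened and the stated detectable difference is not contradicted. The change is worth making because the size term cost no simulated power when size was irrelevant.

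**What to change.** In 7.5, add the blocking variable to the primary model for both outcomes as one continuous fixed effect: the log of the clinic's number of eligible patients at randomisation. Where the effect is read from intervention-by-time, also add log size by time, because a size main effect alone does not sharpen that contrast. Where follow-up is modelled with baseline as a covariate, the main effect is enough. Report a model with block effects as a sensitivity analysis only.

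Name the blocking variable in the same words in sections 2, 3.1, 4.2 and 7.2.1. Section 7.2.1 leaves room for a different blocking scheme; if one is used, the term should be the variable actually used.

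The cost is a sentence or two and one between-clinic degree of freedom (16 to 15). The clinic counts already exist, since the randomisation needs them. The downside is that the term will gain little if the block effect is not roughly linear in size.

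### The intervention-by-time model in section 7.5 has clinic and patient random effects but no clinic-by-time effect, so the PIM test can be anti-conservative; the baseline handling conflicts, and a plain Poisson variance fits the counts poorly

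*Protocol*

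**What the plan says.** Section 7.5 (Data Analyses) specifies multilevel models: "The models will include random effects for clinic and fixed effects for intervention versus delayed control and time (baseline or 1-year"). Later in the same paragraph it adds patient indicators as random effects for the primary analyses, which cover members eligible at baseline or at follow-up. Change in medication use comes from models of follow-up outcomes that "adjust for baseline medication use and estimate change by including an interaction term for intervention by time". On distributions, for change in the number of chronic medications, "we expect to use Poisson regression mixed models while for change in the proportion of patients on PIMs" nonlinear mixed models are planned. No clinic-by-time random effect, dispersion parameter or robust variance is named.

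On design, section 2 says "Clinics will be randomized in blocks of two based on the number of eligible patients per clinic", and section 7.2 says "There will be 9 intervention clinics and 9 control (delayed intervention clinics"). Sections 2 and 2.1 require at least 5 chronic medications for eligibility.

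**The concern.** An intervention-by-time interaction compares change within clinics between the arms. A clinic intercept is common to both time points and drops out of that comparison. So does a patient intercept for anyone measured twice. What remains is within-patient noise plus any tendency of whole clinics to change differently, and the stated model has no term for the second part. Clinics are randomised, so clinic-level change is exactly the variation against which the effect should be judged. Leaving it out treats roughly 3,700 patients as independent sources of information on change when there are 18 clinics. For the PIM outcome the risk is a false positive on a primary endpoint.

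Two further problems sit in the same paragraph. With time coded as baseline or one year, baseline medication use is an outcome row. The text also adjusts for it as a covariate, and both cannot hold in one model. And a Poisson model sets the conditional variance at no less than the mean, which is doubtful for a count that starts at 5 and is measured repeatedly in the same people.

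**Working it through.** **Inputs from the protocol (section 7.2).** "We identified 3,671 eligible members with numbers per clinic ranging from 60 to 350", so m = 3,671/18 = 203.9 per clinic and 1,835.5 per arm. The count power is "given event rate of 6.8 and intraclass correlation coefficient (ICC)=0.01". PIM proportions are 35.8% (control) and 29.0% (intervention).

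**Inputs the protocol does not give, varied here.** The within-patient correlation r (0.5 to 0.9); the between-period correlation c of the clinic effect (1, 0.9, 0.8, 0.5); the true variance s² of the count. The ICC of 0.01 is stated for counts and is assumed for PIMs. Alpha is assumed to be 0.05 two-sided.

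**The plan's own power figure.** It says "we will have > 80% power to detect a decrease of -0.70". Design effect = 1 + 202.9 × 0.01 = 3.03. SE = √[(6.8 + 6.1) × 3.03/1,835.5] = 0.146. Then z = 0.70/0.146 = 4.8 and power is 99.8% (99.4% with t on 16 df). The bound is true but loose; the difference detectable with 80% power is about 0.41. This is a single-time-point comparison, so it neither supports nor refutes the point about the interaction model.

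**PIM interaction, linear analogue.** The true variance is proportional to (1 − r) + m × ICC × (1 − c). With clinic and patient intercepts only, the model variance is proportional to (1 − r). So

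model SE / true SE = √{(1 − r) / [(1 − r) + m × ICC × (1 − c)]}

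and the actual type I error is 2 × [1 − Φ(1.96 × ratio)].

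Example, c = 0.9 and r = 0.5: m × ICC × 0.1 = 0.204; ratio = √(0.5/0.704) = 0.84; error = 9.9%. With r = 0.9: ratio = √(0.1/0.304) = 0.57; error = 26%.

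| c | ratio, r 0.5 to 0.9 | type I error |
|---|---|---|
| 1 | 1.00 | 5% |
| 0.9 | 0.84 to 0.57 | 10-26% |
| 0.8 | 0.74 to 0.44 | 15-38% |
| 0.5 | 0.57 to 0.30 | 26-56% |

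Simulation under the null (18 clinics of 204, linear change scores) gave 14%, 22% and 26% for (c, r) = (0.9, 0.7), (0.8, 0.7) and (0.8, 0.8). A clinic-level analysis of change with t on 16 df gave 4.5-5.5%.

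To judge whether c = 0.9 is extreme: total PIM variance at 35.8% is 0.358 × 0.642 = 0.230. The SD of clinic-level change is √(2 × 0.1 × 0.01 × 0.230) = 0.021. So c = 0.9 means that clinics' one-year changes differ with an SD of about 2.1 percentage points; c = 0.8 means about 3.0 points. The planned effect is 35.8 − 29.0 = 6.8 points.

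**Count variance.** A count of at least 5 with mean 6.8 has variance 1.8 if it is 5 plus a Poisson(1.8), 3.0 if it is a Poisson truncated at 5, and 1.8 × 2.8 = 5.0 if it is 5 plus a geometric. All are below the Poisson 6.8.

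**Count interaction.** The Poisson SE is about √(4 × 6.8/1,835.5) = 0.122 medications. Against the true variance,

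model SE / true SE = √{6.8 / [s²(1 − r) + m × 0.01 × 6.8 × (1 − c)]}

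Example, s² = 3.0, r = 0.7, c = 0.9: √[6.8/(0.90 + 1.39)] = 1.7.

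| c | ratio, s² 1.8 to 5.0, r 0.5 to 0.9 |
|---|---|
| 1 | 1.64 to 6.15 |
| 0.9 | 1.32 to 2.08 |
| 0.8 | 1.13 to 1.52 |
| 0.5 | 0.85 to 0.98 |

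Follow-up counts are not truncated and could be more variable. With s² = 6.8 the ratio is still 1.05 to 1.81 at c = 0.8 to 0.9.

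**The case against.** The strongest reply is that section 7.5 can be read as a model of follow-up outcomes adjusted for baseline. Under that reading the clinic intercept does capture clinic variation at follow-up and the main point falls away. But such a model has no baseline-to-one-year time factor, and so no interaction with it, while the text states both. The reading does not remove the need to correct the section.

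A second reply is that covariance structure, dispersion and degrees of freedom belong in an SAP, which is not at hand, and that the Poisson model is only expected. That stands for details the protocol leaves open. It does not cover what the protocol itself states: the effect parameter, the time coding and the random effects. Followed literally, these can give invalid inference.

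A third reply is that c and r appear nowhere in the protocol, that the calculation pairs every patient although the primary set includes members with one time point only, and that a linear analogue stands in for a binary model. All of this is fair. The sizes are illustrations, not estimates for this trial.

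Three stronger readings are tempting and should not be drawn:

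- A reader might infer that there is only a clinic random effect. Section 7.5 also names patient effects, and the PIM conclusion depends on them. With a clinic effect alone, the PIM standard error would be too large at c = 0.8 or above (ratio 1.05 to 3.16).
- A reader might infer that the count standard error is far too large, so that the two primary outcomes err in opposite directions. The missing clinic-by-time variance pulls the count error the other way, and at c = 0.5 the ratio is below 1.
- A reader might infer a serious loss of power for counts. At the planned 0.70, the Poisson SE gives 0.70/0.122 = 5.7, and power stays above 99.9%. Only effects much smaller than planned would suffer.

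The size blocks are also not named as a model term. Sections 7.2.1 and 7.5 allow covariate adjustment, and no false-positive harm follows from this omission, so it is a lesser matter.

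**Conclusion.** The point holds in this form. The interaction test with clinic and patient intercepts omits clinic-level variation in change, and the PIM standard error is too small whenever the between-period clinic correlation is below 1. At an assumed correlation of 0.9, nominal 5% becomes roughly 10-26%; at exactly 1 the test is correct. The direction follows from the stated model. The size rests on assumed values of c and r and on carrying the count ICC over to PIMs. Separately, baseline cannot be both an outcome row and a covariate, and this conflict is in the text whatever the variance values. For counts, the plain Poisson standard error is usually too wide, by about 1.1 to 2.1 times at c = 0.8 to 0.9, but this reverses if clinic-by-time variation is large, and the planned effect keeps its power.

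**What to change.** State one coherent model per primary outcome in section 7.5. Either of these would do:

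1. Regress the follow-up value on arm, the patient's own baseline value and the clinic-size blocking variable, with a clinic random intercept. Drop the time factor and the interaction.
2. Keep baseline and follow-up as repeated outcomes with the interaction and the clinic and patient effects, remove baseline as a covariate, and add a random clinic-by-time effect.

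Option 1 needs both values for each patient, which section 7.5 currently treats as a secondary set; option 2 keeps members with one value. In both, use small-sample inference based on 18 clinics. For counts, use a linear model, a Poisson mean with estimated dispersion, or a cluster-robust variance with small-sample correction.

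The cost is a change of wording and of model call; no new data are needed. The PIM interval becomes somewhat wider: under option 2 with c = 0.9, about 1/0.84 = 1.2 to 1/0.57 = 1.7 times, plus a t quantile in place of 1.96. That extra width is the clinic-level uncertainty that the present model leaves out.
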